### Outcome Measures

Primary outcome measure is the modification from baseline to month 6 in Treg number in transplanted ALS patients compared to the control arm (26).

Secondary outcome measures include the following:

✓ Biological outcome measures:–Change from baseline to month 3, 6, 9, 12 of the T cell distribution especially the ratio Treg/Th1 or Treg/Th17 comparing FMT arm and control arm (both blood—at each time point, and small intestine—only at 6 and 12).–Changes from baseline to month 3, 6, 9, 12 in inflammatory status (cytokine profile) comparing FMT and control arm (in blood and feces at each time point, and in CSF at month 6).–Changes from baseline to month 3, 6, 9, 12 between FMT arm and control arm in the following biomarkers: creatinine, albumin, CK, vitamin D, plasma/CSF neurofilament heavy/light chain protein.–Biological modifications from baseline to month 6 and 12 in the composition of saliva, gut and fecal microbiota (including SCFA) comparing FMT and control arm.✓ Safety: will be assessed in FMT and control arm considering the occurrence of AEs and modifications in physical examination, vital signs, body weight, and laboratory tests (biochemistry, hematology) during and following the treatment.✓ Clinical outcome measures:The following clinical variables will be compared between FMT and control arm:– Change from baseline to each time point (month 1, 3, 6, 9, 12) of ALSFRS-R.– Survival from onset and randomization to death or tracheotomy.– Change of Forced Vital Capacity (FVC) from baseline to each time point (month 1, 3, 6, 9, 12).– Frequency of procedures (PEG, NIV, IV) from baseline to month 3, 6, 9, 12.✓ Quality of life: will be assessed as the change in absolute and relative values of the Amyotrophic Lateral Sclerosis Specific Assessment Questionnaire (ALSAQ40) from baseline to month 6 and 12 in FMT and control arm.

The Table 3 shows the study flow chart.

**Table 3 T3:** Study flow chart.

	**Pre-treatment**		**Treatment**					**Follow up**			**Study end**
**Examinations**	**Screening**	**Baseline (W0)**	**FMT 1 (Rome)**	**M1**	**M3**	**M6**	**FMT 2 (Rome)**	**M7**	**M9**	**M12 (Rome)**	**M12**
**Time window**		** <3 weeks from screening**	** <4 weeks from screening**	**±3 days**	**±3 days**	**±3 days**	**±7 days**	**±7 days**	**±7 days**	**±7 days**	**≥7 days <4 weeks from M12**
Informed consent	x										
Medical history	x										
Inclusion exclusion criteria	x										
Patient able to understand and follow procedures	x										
FMT			x				x				

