### Interventional Methods

Treatment will be double blinded to patients and neurologists, but not to the endoscopist and microbiologist. ALS patients will undergo upper GI endoscopy with small-intestine biopsies (*n*° 4 biopsies of small intestine, performed with a standard biopsy forces) at baseline and after 6 and 12 months. At baseline, the patients will be randomized (2:1) to either an allogenic (from donors) infusion of collected feces (60 grams) (FMT) in the duodenum-jejunum or no treatment (control group). The infusion will be performed through a standard nasojejunal tube that will be placed during endoscopy. Fecal infusion will be repeated at month 6. Control group patients will not receive any treatment (at baseline or at month 6), but will remain blind to treatment because of sedation due to small-intestine biopsies. Fecal microbiome will be diluted in saline solution (200 ml) and infused at 30 ml/min speed (whole amount of the performance: 15 min). Fresh feces for the FMT will be obtained by habitual healthy donors for *Clostridium difficile* infection. The Table 2 shows the blood and stool testing for donators and the general selection criteria. Before preparation, sample donation will be always analyzed by rapid molecular test to detect intestinal pathogens.

**Table 2 T2:** Criteria for donors' selection.

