### Adverse Events and Safety

According to Directive 2004/23/EC (implemented in Italy with D.Lgs 191/2007):

– “Serious adverse event” (SAE) means any untoward occurrence associated with the procurement, testing, processing, storage, and distribution of tissues and cells that might lead to the transmission of a communicable disease, to death or life-threatening, disabling, or incapacitating conditions for patients or which might result in, or prolong, hospitalization, or morbidity (https://www.hta.gov.uk/policies/human-application-adverse-event-and-reaction-saears-reporting; http://www.sc-toolkit.ac.uk/displaycontent.cfm?widCall1=customWidgets.content_view_1&cit_id=84).– “Serious adverse reaction” (SAR) means an unintended response, including a communicable disease, in the donor or in the recipient associated with the procurement or human application of tissues and cells that is fatal, life-threatening, disabling, incapacitating, or which results in, or prolongs, hospitalization or morbidity (https://www.hta.gov.uk/policies/human-application-adverse-event-and-reaction-saears-reporting; http://www.sc-toolkit.ac.uk/displaycontent.cfm?widCall1=customWidgets.content_view_1&cit_id=84).

The existing studies suggest that FMT is a safe therapy, with few serious adverse events reported. There have been individual reports of peripheral neuropathy, Sjogren syndrome, idiopathic thrombocytopenic purpura, microscopic colitis, contact dermatitis, rheumatoid arthritis, obesity, bacteremia, and ulcerative colitis flare after FMT (24). In one meta-analysis, the overall incidence rate of adverse events after FMT was 28.5%. The commonest FMT-attributable adverse event was abdominal discomfort; also diarrhea, transient fever, nausea, vomiting, and constipation were other common symptoms associated to FMT (24, 28–31).

For these mild adverse events, investigators will treat symptoms according to the usual clinical practice. In case of symptoms that could be considered severe or life threating, the investigator will have to inform the sponsor immediately (within 24 h by fax using a SAE form) and second FMT round may be avoided accordingly to the local investigator's judgment. In accordance with the legislative requirements, Centers will be requested to report immediately from their awareness any SAE or SAR occurring during the trial and coordinating center will send Completed forms by email to Italian National Transplantation Center (CNT).

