### Role of Participating Centers

This multicenter study will involve nine Italian Units: six referral ALS Centers (located in Florence, Chieti, Perugia, Modena, and Rome), three renowned laboratories, one endoscopy service and a statistical unit.

ALS is a rare disease with fast progression and no effective treatment, which requires a solid methodological, clinical approach, and biological background for clinical trials conduction.

Each clinical center is expected: (I) to randomize at least seven patients according to including and excluding criteria in 18 months; (II) to provide one principal investigator to evaluate including and excluding criteria, and assess primary and secondary outcomes; (III) to adhere to ALS management guidelines of the European Federation of Neurological Societies(in particular as regards ventilation and nutrition issues).

The analysis of biomarkers will be centralized and performed in two internationally renowned laboratories Laboratory of Microbiology Policlinico Gemelli in Rome and Laboratory of Immunology, Department of Experimental and Clinical Medicine—University of Florence, and FMT will be performed at Policlinico Gemelli in Rome, a leading European Center for this kind of treatment.

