### Data Analysis

Data will be collected by investigators through electronic CRF, which will be conveyed to the trial database. At trial completion, data from the locked database will be extracted for analysis by an expert statistician.

Separate analyses will be performed in:

All randomized subjects receiving at least 1 FMT (Intention-to-treat population).All randomized subjects excluding protocol deviations (Per protocol population).

As far as biological activity is concerned, immune response to FMT will be analyzed as a difference in positive response to FMT between the control group and the FMT group, assessed by comparison of proportion of patients in the two groups showing a mean Tregs increase by at least 20%, between baseline and month 6 measurements.

Mean values of different T, B, NK cell subpopulations, neurodegeneration biomarkers, and cytokines will be assessed and mean differences in plasma concentrations between the two treatment arms will be calculated using *t*-test or Wilcoxon-Mann-Whitney test as previously reported (26). ANOVA will be used for assessing the mean change over time for the same variables as above, with treatment as between-subjects factor and time as within-subjects factor. Different models will be used, each with a different biomarker of activity as the dependent variable. Models will be adjusted for any unbalanced distribution of the main prognostic factors (e.g., age) between the two treatment arms, according to previously published statistical methods (26).

Analysis of microbiota will be performed with specific software.

Record of any AE and SAE will be kept for every subject receiving at least one round of FMT till the study completion, performing safety analysis accordingly.

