As for clinical outcome measures, we will compare ALSFRS-R total score and subscores (bulbar, respiratory, gross, and fine motor) changes from baseline to each time point in treatment arm vs. control arm. Frequency of procedures (PEG, NIV, IV) will be compared from baseline to each time point in treatment vs. control arm. The comparison of clinical endpoint among arms will be carried out by using the logistic regression model. Results will be presented as odds ratios (OR) and 95%C.I. FMT will be considered effective in relation to controls whether the OR of positive results will provide a *p* < 0.05. Change in FVC during the study will be analyzed using a mixed model for repeated measures (MMRM). Difference between treatment groups and two-sided 95% CI will be estimated .Log-rank tests via Kaplan-Meier method will be employed to compare differences in tracheostomy-free survival between the two treatment arms (from onset and from randomization), while Cox's proportional hazard model will be used for adjusting for any possible unbalanced prognostic factors. Statistical significance will be set at 0.05 level for a two-tailed test. Last observation will be considered for patients with missing data.

Given the short duration of the study, an interim analysis of efficacy data is not scheduled. Nevertheless, to address safety concerns, a report including all relevant clinical data of patients will be sent by the Statistics Unit to an independent Data and Safety Monitoring Board for scheduled DSMB meetings (also through Skype) when 14 patients would have completed the second treatment and then every 6 months.

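### Month 6, the primary time point, has no Treg draw outside Rome: a patient who misses FMT 2 (Rome) has no scheduled primary value, although the M6 visit already takes blood

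*Protocol article*

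**What the plan says.** The Outcome Measures section sets the primary outcome: "Primary outcome measure is the modification from baseline to month 6 in Treg number in transplanted ALS patients compared to the control arm". Data Analysis compares the proportions of patients whose Treg rises by at least 20% between baseline and month 6.

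Table 3 (study flow chart) ticks Treg at Baseline, FMT 1 (Rome), M3, FMT 2 (Rome), M9, M12 (Rome) and the final M12 visit. The M6 cell is empty. The same M6 column is ticked for hematology, biochemistry, peripheral biomarkers and CSF. The windows are ±3 days for M3 and M6, and ±7 days for FMT 2 (Rome).

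Three other statements bear on a missed Rome visit:

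- Adverse Events and Safety: after severe symptoms the "second FMT round may be avoided accordingly to the local investigator's judgment".
- Data Analysis, on the analysis set: "All randomized subjects receiving at least 1 FMT (Intention-to-treat population".
- Data Analysis, on missing values: "Last observation will be considered for patients with missing data".

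Interventional Methods schedules endoscopy with biopsies for both arms, "performed with a standard biopsy forces) at baseline and after 6 and 12 months". The Rome visit at month 6 is therefore planned whether or not the patient receives an infusion.

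**The concern.** The primary comparison depends on a single sample per patient at month 6, and that sample is tied to a visit that requires travel to Rome and a sedated endoscopy. A patient with early-stage but progressive ALS might attend the home-centre M6 visit and not travel, or might miss Rome for another reason. No Treg value is then scheduled at the primary time point. The last-observation rule would not leave the value missing. It would enter the M3 result as if it were month 6.

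The responder endpoint turns each such substitution into a yes or no that may differ from what month 6 would have shown. An analysis plan cannot repair this later, because it cannot recover a sample that was never drawn.

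**Working it through.** **Is month 6 the exception?** The Treg row of Table 3, grouped by the three Rome time points:

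| Time point | Rome visit | Treg there | Adjacent non-Rome visit | Treg there |
|---|---|---|---|---|
| Month 0 | FMT 1 (Rome) | yes | Baseline | yes |
| Month 6 (primary) | FMT 2 (Rome) | yes | M6 | no |
| Month 12 | M12 (Rome) | yes | M12, study end | yes |

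Month 6 is the only one without a second draw. Treg is also taken outside Rome at M3 and M9, so collection away from Rome is already part of the plan.

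**How old would the substitute be?** Take 3 months as 91 days, with M3 at ±3 days and FMT 2 (Rome) at ±7 days.

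- Shortest gap: 91 − 3 − 7 = 81 days.
- Longest gap: 91 + 3 + 7 = 101 days.

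**What does it do to the response rate?** The Sample Size Estimation section plans 50% responders on FMT against at most 5% in controls, with 28 and 14 patients. The protocol gives no rate of missed Rome visits. As an assumption, take 1 to 3 of 28 treated patients; 3 is close to the stated 10% drop-out (0.10 × 28 = 2.8).

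- One treated substitution moves the FMT rate by up to 1/28 = 3.6 percentage points; three move it by up to 3/28 = 10.7.
- All carried values non-responses: 27 × 0.5 / 28 = 48.2% (one patient); 25 × 0.5 / 28 = 44.6% (three).
- All carried values responses: (27 × 0.5 + 1) / 28 = 51.8% (one); (25 × 0.5 + 3) / 28 = 55.4% (three).
- One substitution in a control moves the control rate by up to 1/14 = 7.1 points.

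**What does it do to power?** The article names no test for the two proportions, so a two-sided Fisher exact test at 0.05 is assumed. With k treated values fixed as non-responses, treated responders follow a binomial(28 − k, 0.5) and control responders a binomial(14, 0.05). Power is the total probability of the significant tables that favour FMT.

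The planned 0.80 is met first: the stated 39 patients, split 26 and 13, give 0.867. With 28 and 14:

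| Treated values carried as non-responses (k) | Power |
|---|---|
| 0 | 0.906 |
| 1 | 0.884 |
| 2 | 0.857 |
| 3 | 0.825 |

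These figures cover substitutions in the treated arm only.

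**Does the order of M6 and FMT 2 matter?** Their windows (±3 and ±7 days) overlap around the same nominal date. FMT 2 could therefore fall up to 3 + 7 = 10 days before M6. An added M6 draw should be placed before FMT 2 so that it always precedes the second infusion.

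**The case against.** The strongest reply is that the primary value is scheduled. FMT 2 (Rome) is the month-6 visit, and Treg is drawn there together with gut tissue, stool and saliva. On this view a second draw is a preference. That stands in part: the plan does not omit its primary outcome. What it lacks is the back-up that it provides around months 0 and 12.

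A reader might infer that treated patients with FMT toxicity would lose their month-6 value while controls would not, so that any bias is confined to one arm. The text does not support this. It allows the infusion round to be avoided, not the visit, the endoscopy or the blood draw, and controls attend Rome without any infusion. Interventional Methods also blinds neurologists as well as patients, who "will remain blind to treatment because of sedation due to small-intestine biopsies". A blinded investigator could withhold the second round for a control with severe symptoms.

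The figure of 3 in 28 is also generous. Drop-outs would often miss the M6 visit too, and an M6 draw would not rescue them.

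A reader might further infer from Table 3 that month 12 is unsafe. FVC, hematology and biochemistry are blank at M12 (Rome) and return only at the final visit, "≥7 days <4 weeks from M12". The blank cells are real. But a condensed article may leave the pre-sedation work-up to the full protocol or the endoscopy service, vital signs and physical examination are ticked at M12 (Rome), and no harm is shown. Moving those tests earlier would also give up routine bloods after the last endoscopy. That is a trade-off and not part of this point.

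**Conclusion.** The gap holds, as a cheap improvement and not as a flaw that undermines the design. At the primary time point a patient in either arm who attends M6 but misses FMT 2 (Rome) has no scheduled Treg value, and the stated rule would use one about 81 to 101 days older.

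How often this would happen is unknown. Under the assumed 1 to 3 of 28 treated patients, with every carried value a non-response, the loss of power is modest and the planned level is still met. Carried values could equally be responses, so the direction of any bias cannot be stated. These results rest on the assumed count, the assumed Fisher test and a 91-day quarter. They also assume that controls are in the main analysis, as the comparison requires, even though the stated analysis set is worded around receipt of FMT.

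**What to change.** - In Table 3, add a Treg draw at M6 for all patients, and state that the M6 visit precedes FMT 2 (Rome). Drawing from everyone is necessary because nobody can reliably know at M6 who will later miss Rome.
- State that the Rome sample is the month-6 primary value when present, and that the M6 sample is used when it is missing.
- State that a patient whose second infusion is withheld still gives the month-6 Treg sample and stays in follow-up in the assigned arm.

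The cost is one extra tube, its transport and one assay for up to 42 patients. No visit is added, since M6 already takes blood. Central handling is already planned ("The analysis of biomarkers will be centralized and performed in two internationally renowned laboratories"), and Treg is already collected outside Rome at M3 and M9.

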**CLINICAL ASSESSMENT**											
Neurological examination	x	x		x	x	x		x	x		x
ALSFRS-R	x	x		x	x	x		x	x		x
FVC	x	x		x	x	x		x	x		x
MRC	x	x		x	x	x		x	x		x
BMI	x	x	x	x	x	x	x	x	x	x	x
**SAFETY ASSESSMENT**											
Adverse events		x		x	x	x		x	x		x
Vital signs	x	x	x	x	x	x	x	x	x	x	x
Physical examination	x	x	x	x	x	x	x	x	x	x	x
Concomitant medications	x	x	x	x	x	x	x	x	x	x	x
Chest X-ray	x (1)										
ECG	x (1)										
Hematology	x	x		x	x	x			x		x
Biochemistry	x	x		x	x	x			x		x
Urinalysis	x	x		x	x	x			x		x
Pregnancy test	x										
Infectious markers	x										
Fecal calprotectin			x				x			x	

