The coordinating Center will be responsible for appropriate AE reporting to the regulatory authorities (CNT) every 6 months; investigators will be responsible for reporting to appropriate Ethic Committee. In case of death, a clinical report will be prepared by the caring investigator together with SAE form; in case of autopsy, autopsy report will be added to study documentation.

The trial will be stopped in case of 30% excess in the treating group of the following AEs: peritonitis, upper gastrointestinal hemorrhage, sepsis, bacteremia. Instead, the next toxicities will be considered acceptable: diarrhea, abdominal cramping and pain, nausea, vomiting, flatulence, fever, constipation, dizziness, sore throat, rhinorrhea, bloating, nasal stuffiness, urinary infections, headache, mild/moderate blood cells alterations; elevated CRP, rashes, urticaria, dermatoses, dermatitis (mild/moderate severity), elevated aminotransferase/alkaline phosphatase, loss of appetite, colitis/gastroenteritis.

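### Table 3 schedules no adverse-event assessment at the three Rome endoscopy visits, which does not fit the safety outcome promised for both arms and leaves controls least covered

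*Protocol article*

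**What the plan says.** Four places in the protocol article bear on this point.

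- **Table 3, safety block.** The row "Adverse events" is ticked at Baseline, M1, M3, M6, M7, M9 and the final M12 visit. It is blank at Screening, FMT 1 (Rome), FMT 2 (Rome) and M12 (Rome). The row "Physical examination" is ticked at all eleven visits, as are vital signs and concomitant medications.
- **Interventional Methods.** "ALS patients will undergo upper GI endoscopy with small-intestine biopsies" at baseline, month 6 and month 12. This applies to both arms. Controls receive no infusion and are kept blind by the sedation given for the biopsies.
- **Outcome Measures.** Safety is to be assessed in the FMT and control arms "considering the occurrence of AEs and modifications in physical examination, vital signs, body weight, and laboratory tests (biochemistry, hematology) during and following the treatment".
- **Adverse Events and Safety, and Data Analysis.** For symptoms that may be severe or life-threatening, "the investigator will have to inform the sponsor immediately (within 24 h by fax using a SAE form". Centers must also "report immediately from their awareness any SAE or SAR occurring during the trial". Data Analysis adds a record of all adverse events, serious or not, up to study completion, but words it for patients who have had one or more FMT rounds.

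**The concern.** Safety and tolerability are a stated secondary objective, and the article describes this as the first FMT trial in ALS. The events that Adverse Events and Safety lists as common after FMT (abdominal discomfort, diarrhea, transient fever, nausea, vomiting, constipation) are mostly non-serious and short-lived. They are most likely to appear on or just after a procedure day, and on those days the printed schedule asks nobody to assess adverse events.

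What is at stake is the comparison between arms. Both arms have sedation, endoscopy and four biopsies; only one has the infusion. To separate harm from the infusion from harm due to the endoscopy, procedure-day events must be captured equally in both arms. If recording is more complete in FMT recipients, the difference between arms is biased against FMT. If it is thin in both arms, the tolerability description is incomplete.

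**Working it through.** The plan states no figure to reproduce, so the check is a reading of Table 3 against the text, with simple counts.

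**1. Table 3 by column.** The adverse-event row has eleven cells for eleven visit columns, so nothing suggests a shifted or lost tick. At the three Rome visits:

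| Row | FMT 1 | FMT 2 | M12 (Rome) |
|---|---|---|---|
| Gut tissue (endoscopy and biopsy) | x | x | x |
| FMT | x | x | – |
| Vital signs, physical examination, concomitant medications | x | x | x |
| Adverse events | – | – | – |
| Hematology, biochemistry, urinalysis | – | – | – |
| Neurological examination, ALSFRS-R, FVC, MRC | – | – | – |

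The three blanks coincide exactly with the three gut-tissue days. Other rows are blank there too, so the omission is not peculiar to adverse events.

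**2. Which route covers which event on a procedure day?**

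| Arm and event | Scheduled that day (Table 3) | Immediate reporting (Adverse Events and Safety) | Running record (Data Analysis) |
|---|---|---|---|
| FMT, serious | no | yes | yes |
| FMT, non-serious | no | no | yes |
| Control, serious | no | yes (no arm is named) | not in the wording |
| Control, non-serious | no | no | not in the wording |

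The last line has only the general promise in Outcome Measures and no stated route on the day.

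**3. Number of procedures.** Inputs are 28 FMT and 14 control patients and three endoscopies each.

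- FMT: 28 × 3 = 84
- Control: 14 × 3 = 42
- Total: 84 + 42 = 126, of which controls are 42/126 = one third

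This is the maximum at full retention. Sample Size Estimation assumes 10% drop-out, so the actual count would be lower.

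**4. Time to the next scheduled assessment.** The article does not say from which day M1 and M7 are counted. Taking a month as 30 days (assumption):

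- After FMT 1: about 30 days, with ±3 days on M1, if M1 is counted from the infusion. If M1 is counted from randomization and the endoscopy falls at the 21-day limit, 30 − 21 = 9 days, or 6 to 12 days with the ±3-day window.
- After FMT 2: nominally about 30 days. FMT 2 and M7 each carry ±7 days, so 16 to 44 days if the two windows are used independently.
- After M12 (Rome): the final visit is set at "≥7 days <4 weeks from M12". If that refers to the Rome visit, the gap is 7 to 27 days.

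The gap is therefore a range that depends on these assumptions, not one fixed interval.

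**The case against.** The strongest reply is that a tick marks a planned assessment and does not limit when an event may be entered. The article nowhere says that adverse events are taken only at ticked visits. Logging between visits is the kind of detail an article leaves to the full protocol and the e-CRF. The blanks also follow a pattern: from Baseline onward the adverse-event row matches the neurological examination, ALSFRS-R, FVC and MRC rows. That may separate visits to the ALS centers, where neurologists are blinded, from procedure visits in Rome, where the endoscopist is not. The article does not give this reason, but it is plausible.

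Much of this stands, and it rules out three stronger readings that a reader might infer:

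- *Procedure-day events depend on patients' later recall.* The documents do not say so. Patients are examined on those days, and the running record for FMT recipients covers any adverse event.
- *The table singles out adverse events.* It does not; laboratory and neurological rows are blank there as well.
- *Events in the stopping rule would be missed.* The listed events ("peritonitis, upper gastrointestinal hemorrhage, sepsis, bacteremia") would ordinarily be severe enough to be reported immediately, which does not depend on a visit.

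The reply does not remove the mismatch itself. The article prints an explicit visit-by-visit safety schedule, and that schedule, followed as written, contains no adverse-event assessment on the days treatment is given. Nor does it answer the Data Analysis wording, which leaves out controls.

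**Conclusion.** The point holds in a limited form. Table 3 schedules no adverse-event assessment at FMT 1, FMT 2 or M12 (Rome), which is inconsistent with a safety outcome covering both arms during and after treatment. Serious events are covered by immediate reporting. What lacks a scheduled assessment is the non-serious procedure-day event, and the gap is largest in controls, for whom the Data Analysis record is not worded either. The between-arm comparison could therefore rest on uneven capture.

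The size is bounded only in procedures: at most 126 endoscopies, 42 of them in controls. That is not a count of endoscopies without any adverse-event entry. The article gives no rate of non-serious events by procedure day, so the number that might go unrecorded cannot be estimated. The conclusion assumes that the schedule is followed as printed and that the full protocol adds no separate instruction for the Rome visits. This is a minor point that is cheap to correct; it does not affect the primary outcome.

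**What to change.** 1. In Table 3, tick the adverse-event row at FMT 1, FMT 2 and M12 (Rome) for both arms. Staff already present at those visits should make the entry on the existing e-CRF, in the same way in each arm, and in a form that does not reveal allocation to the blinded neurologists.
2. In Data Analysis, reword the adverse-event record and the safety analysis so that they cover all randomized patients, in line with Outcome Measures.
3. Summarise procedure-day adverse events by arm, so that endoscopy-related and infusion-related events can be told apart.

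The cost is one more e-CRF entry at each of three existing visits. The drawback is that the staff making it may know the allocation, so knowledge of treatment could colour what is recorded. Asking the same questions in both arms limits this but does not remove it.
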